## Abstract

**Background:**

Anemia is a risk factor for death, adverse cardiovascular outcomes and poor quality of life in patients with chronic kidney disease (CKD). Erythropoietin Stimulating Agents (ESA) are commonly used to increase hemoglobin levels in this population. In observational studies, higher hemoglobin levels (around 11-13 g/dL) are associated with improved survival and quality of life compared to hemoglobin levels around 9-10 g/dL. A systematic review of randomized trials found that targeting higher hemoglobin levels with ESA causes an increased risk of adverse vascular outcomes. It is possible, but has never been formally tested in a randomized trial, that ESA dose rather than targeted hemoglobin concentration itself mediates the increased risk of adverse vascular outcomes. The Clinical Evaluation of the DOSe of Erythropoietins (C.E. DOSE) trial will assess the benefits and harms of a high versus a low fixed ESA dose for the management of anemia in patients with end stage kidney disease.

**Methods/Design:**

This is a randomized, prospective open label blinded end-point (PROBE) trial due to enrol 2204 hemodialysis patients in Italy. Patients will be randomized 1:1 to 4000 IU/week versus 18000 IU/week of intravenous epoietin alfa or beta, or any other ESA in equivalent doses. The dose will be adjusted only if hemoglobin levels fall outside the 9.5-12.5 g/dL range. The primary outcome will be a composite of all-cause mortality, non fatal stroke, non fatal myocardial infarction and hospitalization for cardiovascular causes. Quality of life and costs will also be assessed.

**Discussion:**

The C.E.DOSE study will help inform the optimal therapeutic strategy for the management of anemia of hemodialysis patients, improving clinical outcomes, quality of life and costs, by ascertaining the potential benefits and harms of different fixed ESA doses.

**Trial registration:**

Clinicaltrials.gov NCT00827021

## Background

Anemia affects almost all patients with end-stage kidney disease (ESKD) receiving renal replacement therapy [1]. Established treatment options for anemia of chronic kidney disease (CKD) are Erythropoietin Stimulating Agents (ESA), including erythropoietins (EPO alfa, beta), darbepoetin (DARBO α), pegylated epoietin (continuous erythropoietin receptor activator, CERA) and biosimilar epoetins. Observational studies suggest that, compared to patients with chronic kidney disease whose haemoglobin (Hb) levels are on average 11 g/dL, CKD patients with Hb levels < 11 g/dL experience a 20-70% higher risk of death and a 20-40% higher risk of hospitalization [2] and CKD patients with Hb levels > 12 g/dL have a 15-20% lower risk of hospitalization with no survival advantage [3]. However these studies, due to their observational design, can only establish an association between Hb and survival, and do not demonstrate a causal relationship between Hb levels and risk of death or hospitalizations.

Randomized clinical studies have consistently shown that Hb targets of 12.0-13.5 g/dL achieved with ESA cause an increase in adverse vascular events compared to Hb levels of 10-12 g/dL achieved with the same agents or no treatment [4-6]. A recent meta-analysis [7], including 9 trials (5143 patients), concluded that patients who achieve Hb targets around 12.5-13.5 g/dL with ESA have a 17% higher risk of death (95% confidence intervals (CI) 1%-35%) compared to those who achieve lower Hb targets (< 12 g/dL) with the same agents. The excess risk of death is mainly due to an increased rate of adverse vascular outcomes (which increased by 25%, 95% CI 9-42%). This meta-analysis was dominated by three large multicenter randomized trials: the "Normal Hematocrit Study" [4] (NHS, n = 1233), which enrolled patients receiving hemodialysis, the "Correction of Hemoglobin and Outcomes In Renal insufficiency" study (5) (CHOIR, n = 1432) and the "Cardiovascular Risk reduction by Early Anaemia Treatment with Epoietin beta" study [6] (CREATE, n = 603) both conducted in patients with CKD not receiving dialysis. These individual studies and their pooled analysis, found that higher Hb targets (13.0-15.0 g/dL) achieved with ESA, compared to giving ESA to achieve lower Hb targets (10.5-11.5 g/dL), caused either an increased risk of death for cardiovascular events (CHOIR: relative risk (RR) 1.34; CI 95%:1.03-1.74) or, at best, no reduction in the risk (CREATE: RR 0.78; CI 95%: 0.53-1.14). In summary, based upon these data, it was concluded that administering ESA to achieve Hb targets > 12.5 g/dL caused an increased risk of all-cause mortality (RR 1.17; CI 95%: 1-13.5; p = 0.031) compared to administering ESA to achieve Hb targets between 9.0 and 12.0 g/dL.

The clinical practice patterns for management of anaemia of CKD still remain highly variable with conflicting recommendations from key guideline agencies relating both to optimal Hb targets (Table 1), ESA administration (including the Hb concentration at which patients should begin ESA treatment or have their ESA dose adjusted), iron management and other aspects of ESA treatment (including definitions of ESA resistance, role of inflammation in management of anaemia, etc.). The variability in clinical practice and guideline statements prompted several systematic reviews and design and conduct of additional randomized trials However, a key question that remains unanswered is what is the mechanism by which higher Hb targets cause harm. The uncertainty regarding optimal anemia management in patients with chronic kidney disease is compounded further by the recent release of the results of the "Trial to Reduce Cardiovascular Events with Aranesp Therapy (TREAT)" [8]. This trial, conducted in 4038 patients with diabetes and early CKD, who were not yet receiving dialysis, found that darbepoetin alfa 'does not beat placebo' for the composite endpoint of survival and non fatal cardiovascular events (RR 1,05; CI 95%: 0,94-1,17; p = 0,41). In addition, darbepoetin alfa may cause harm (significant increase in the risk of stroke, RR 1.92; CI 95%: 1.38-2.68; p < 0,001) with no significant quality of life advantage [5,8].

**Table 1 T1:** Guidelines on hemoglobin (Hb) targets in patients with CKD^a^.

Guidelines	Country	Year	Target Hb level (g/L)
European medicines Agency (EMEA)	Europe	2008	100-120
National Kidney Foundation-Dialysis Outcome Quality Initiative (NKF-DOQI)	USA	2007	110-120
Italian Society of Nephrology	Italy	2006	110-115
			100-105^b^
British Renal Association (BRA)	UK	2006	105-125
Canadian Society of Nephrology (CSN)	Canada	2008	100-120
European Best Practice Guidelines^&^(EBPG)	Europe	2004	> 110^c^
Caring for Australasians with Renal Impairment (CARI)	Australia	2008	< 130^d^

^a ^Hb, hemoglobin; CKD, chronic kidney disease

^b ^In patients with cardiovascular disease

^c ^Hb levels > 120 g/L are not recommended for patients with severe cardiovascular disease unless continuing severe symptoms dictate otherwise

^d ^In many patients Hb of 110 g/L may be a suitable therapeutic target nadir

Taken together, these data showing increased harm and limited evidence for benefit bring anemia management in chronic kidney disease back to its origins. Initially, ESA were introduced to treat anemia in patients with ESKD receiving hemodialysis for renal replacement therapy, and who required red blood cell transfusions to elevate severely reduced hemoglobin levels. Given this identified benefit of ESA treatment, namely a significant reduction in the rate of transfusion [8], the question of potential treatment efficacy was expanded and explored in the pre-dialysis setting where subsequently no beneficial effects and the potential for harm have been clearly demonstrated. In light of the absence of benefit from targeting hemoglobin levels for patients with CKD, it is now important to understand whether alternative therapeutic strategies to manage anaemia in CKD can be found and whether a fixed dose ESA strategy (high or low) might increase hemoglobin levels without signifcant harm (adverse vascular events and mortality).

The mechanism by which targeting Hb levels above 12.5 g/dL causes an increase in the risk of death and cardiovascular events remains uncertain. It is possible that the ESA dose required to achieve and maintain higher Hb targets is directly linked with adverse events, most particularly in patients who are resistant to the actions of administered ESA [9,10]. Further, evaluating differing fixed doses of ESA is difficult because Hb levels inextricably link to ESA dose and demonstrably affect patient outcomes.

### Trial Hypothesis

We will test the hypothesis that fixed doses of ESA are feasible and provide improvements in clinical events and quality of life in individuals with end-stage kidney disease, without increasing adverse outcomes. The Clinical Evaluation of the DOSe of Erythropoietins (C.E. DOSE) trial is the first study to test this hypothesis and assess the feasibility of two therapeutic strategies for the management of anemia in ESKD. The trial has two therapeutic strategies. These are two fixed ESA doses. The first is based on the prescription of a minimum ESA dose (4000 I/U per week) and the second is based on the administration of a maximum ESA dose (18000 I/U per week), independent of the Hb target level which is achieved. Both strategies include a rescue mechanism for dose tapering when Hb levels fall outside the range of 9,5 to 12,5 g/dL.

### Aims of the study

1) To evaluate the comparative efficacy of two fixed ESA doses (high versus low) on a composite of major cardiovascular endpoints and on safety endpoints;

2) to evaluate the effects of two fixed ESA doses on quality of life in hemodialysis patients by means of a validated quality of life assessment tool;

3) to evaluate the feasibility of each of the fixed-dose therapeutic strategies; and

4) to conduct a cost-effectiveness analysis for the two therapeutic approaches.

## Methods/Design

### Study population

Patients > 18 years who fulfil the following criteria:

1) Presence of anemia related to ESKD. Anemia is defined by the National Kidney Foundation as having a Hb level below 12.0 g/dL in women and 13.5 g/L in men. In the interest of a common definition for recruitment in the C.E. DOSE trial, any patient who is already receiving ESA will be eligible for randomization, as well as any patient in which the managing physician would initiate ESA treatment. Patients will be excluded if they have a Hb > 10 g/dL and are not currently receiving ESA treatment. For these individuals, ESA initiation would not be recommended based on current evidence;

2) Renal replacement therapy with hemodialysis (bicarbonate dialysis, hemofiltration, hemodiafiltration, on-line hemodiafiltration, or acetate-free biofiltration);

3) No contraindication to ESA treatment.

Patients who are already receiving treatment with any ESA may participate in the trial and will be directly enrolled and randomized into the trial without a wash-out period. This study will be conducted in agreement with the Declaration of Helsinki. Patients will provide written informed consent before commencement of the study. The following Ethics Committee approved the study: Comitato indipendente di etica medica dell'AUSL BR/1 di Brindisi, Italy.

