### Study design

This will be a pragmatic, multicenter, centrally randomized, controlled trial (Figure 1) based upon the intention-to-treat principle. To achieve allocation concealment, randomization will be carried out centrally by the coordinating study center. Independent of baseline Hb level, participants will be allocated to ESA 4000 IU/week intravenously versus 18000 IU/week intravenously of erythropoietin alfa, beta, or equivalent doses of any other commercially available agent (including darbepoetin alfa, C.E.R.A. or biosimilars and other agents, which may become available). Randomization will be stratified by enrolling center and treatments will be assigned by random permuted blocks of six patients.

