**Figure 1 F1:**
[figure not shown]
**Flow chart describing the selection, randomization and follow-up process of the Clinical Evaluation of the Dose of Erythropoietins (C.E. DOSE) trial**.

As there are no previous studies relating to the benefits/harms of different ESA doses for the anemia of ESKD, we established two fixed experimental doses according to the following criteria, based upon available data:

1. In the antecedent Hb target trials conducted in CKD patients [4-6], patients randomized to high (12-14 g/dL) and low (9.5-11.5 g/dL) Hb targets received between 20000 to 30000 IU/week and between 0 to 10000 g/dL IU/week of EPO, respectively.

2. In the 2004 United States Renal Data System report, 50% of hemodialysis patients incident to ESRD therapy in 1998 and followed for one year, had Hb levels between 10-13 g/dL and received more than 13000 IU/week of EPO, in particular 25% received from 13.944 to 21692 IU/week and 25% more than 21.692 IU/week of EPO [11].

Based on these assumptions the two selected experimental doses will maximize study efficacy. We will also have a safety mechanism within the trial to ensure that, after allocation to treatment, Hb values do not fall outside the safety range (of 9.5 g/dL-12.5 g/dL). A hemoglobin value above or below this range will trigger a change in the ESA dose. The prescribed ESA dose will be gradually increased or decreased by 25% until Hb values return to between 9.5 and 12.5 g/dL.

We expect recruitment to last 12 months and follow-up will be completed after 1194 cardiovascular events have occurred, which is expected to be approximately 4 years after the last patient is enrolled.

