#### Data analysis

Analysis will be by the intention-to-treat principle. The incidence rate of events in the high dose versus the low dose ESA groups will be estimated using Kaplan-Meier curves. Log-rank test will be used to compare the two curves [17].

Additional multivariate analyses will be performed using a Cox proportional hazards model [17]. The proportional hazards assumption will be checked by graphical inspection of log (-log [survival]) plot. Analyses will be performed for assessment of the efficacy of study interventions (high doses or low doses of ESA) on any of the end-points of this study, including quality of life and costs. The treatment effect on outcomes, quality of life, and costs will be also evaluated through subgroup-analysis based upon a series of potential effect modifiers (baseline information) including socio-demographic factors (gender, age, ethnicity, marital status, education, occupational status), presence or absence of cardiovascular risk factors (diabetes mellitus, hypertension, cigarette smoking, family history of cardiovascular disease), presence or absence of previous major cardiovascular event, presence or absence of other major concomitant illness, type of ESA administered, average ESA dose administered during the study, metabolic control (quartiles of total/LDL/HDL-cholesterol and HbA1c), other cointerventions (iron, vitamin D or vitamin D analogues, phosphate binders, calcimimetics, antihypertensive agents, statins, anticoagulants), baseline and end of treatment levels of calcium, phosphorus, iron, parathyroid hormone; Kt/V, dry weight, dialysis blood flow rate, interdialytic weight gain, type of dialysis (bicarbonate-dialysis, high versus low flux, hemodiafiltration, online hemodiafiltration, hemofiltration, acetate-free biofiltration), dialysis duration (minutes per dialysis session) and dialysis vintage (months). Existing trends in the efficacy based upon these subgroup analyses will be tested with the Mantel-Haenszel test for each of these covariates. A chi-square test will be used to assess heterogeneity of observed effects of interventions.

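### The effect-modifier list is labelled baseline, but its only ESA dose variable is measured after randomization; prior ESA dose or status and baseline hemoglobin are not named

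*Protocol article*

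**What the plan says.** The protocol article defines a broad population. The *Study population* section puts entry this way: "any patient who is already receiving ESA will be eligible for randomization, as well as any patient in which the managing physician would initiate ESA". The one hemoglobin limit concerns untreated patients: "Patients will be excluded if they have a Hb > 10 g/dL and are not currently receiving ESA treatment". Patients already on an ESA "will be directly enrolled and randomized into the trial without a wash-out period", and no limit is set on their current dose.

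Under *Study design*, patients are allocated to 4000 or 18000 IU/week, or an equivalent, whatever their starting hemoglobin. The dose then changes in 25% steps when hemoglobin leaves 9.5-12.5 g/dL. On allocation: "Randomization will be stratified by enrolling center and treatments will be assigned by random permuted blocks of six patients". The *Trial Hypothesis* sets a minimum-dose strategy against a maximum-dose one: "the second is based on the administration of a maximum ESA dose (18000 I/U per week"). To justify the doses, *Study design* cites US registry patients, of whom 25% received 13944 to 21692 IU/week and "25% more than 21.692 IU/week of EPO" (the point is a thousands separator).

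The *Data analysis* section then plans a "subgroup-analysis based upon a series of potential effect modifiers (baseline information"). The list is long and reaches marital status, blood flow rate and session length. Its ESA items are the type of agent and the mean dose received while on study. It does not name baseline hemoglobin, the dose before randomization, or whether the patient was on an ESA at entry. Trend across subgroups is to be tested by Mantel-Haenszel and heterogeneity by chi-square.

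The *Background* suggests that the dose needed to reach higher hemoglobin targets may itself be linked to harm, "most particularly in patients who are resistant to the actions of administered ESA".

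**The concern.** An effect modifier has to be fixed before randomization. Otherwise the patients compared within a stratum are no longer a randomized comparison. Mean on-study ESA dose is the assigned treatment plus the patient's response to it. Stratifying on it conditions on the intervention the trial is testing.

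In an ESA dose trial, readers would turn first to the table of effect by dose to see who is harmed. Built as listed, it could show a trend produced only by how patients came to their doses. The question that randomization can answer, whether the effect differs by the dose and hemoglobin a patient had at entry, is not among the named analyses. Broad entry makes that question relevant: the same allocated dose is a first prescription for one patient, an increase for another and a reduction for a third.

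**Working it through.** **1. The plan's event target.** Step 5 uses the target of 1194 events, so it is checked first. With a hazard ratio of 0.85, 80% power and alpha 0.05 (two-sided assumed), Freedman's formula gives ((1 + 0.85)/(1 − 0.85))² × (1.960 + 0.842)² = 152.1 × 7.849 = 1194. The figure reproduces exactly.

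**2. When each variable is fixed.**

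| Variable | Fixed when | Named as a modifier? |
|---|---|---|
| Mean on-study ESA dose | After randomization, by arm and hemoglobin response | Yes |
| ESA dose before randomization | At entry | No |
| On ESA or untreated | At entry | No |
| Baseline hemoglobin | At entry | No |

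**3. Who would fall in a stratum of on-study dose.** The starting doses differ by a factor of 18000/4000 = 4.5. Patients who stay near their allocated dose therefore fall in strata made up of one arm only, where there is nothing to compare.

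The arms meet only after several steps. If each 25% step compounds, three steps down in the high arm give 18000 × 0.75³ = 7594 IU/week, and three steps up in the low arm give 4000 × 1.25³ = 7813 IU/week. If each step is 25% of the allocated dose, two steps down give 18000 − 2 × 4500 = 9000 and five steps up give 4000 + 5 × 1000 = 9000.

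On either reading, a middle stratum would compare high-arm patients whose hemoglobin repeatedly exceeded 12.5 g/dL with low-arm patients whose hemoglobin repeatedly fell below 9.5 g/dL. These are good responders against poor responders. The contrast mixes dose with responsiveness, and no test of trend or heterogeneity across such strata removes that.

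**4. How mixed the entry doses could be.** Take the US figures at face value, assuming that entrants resemble those patients:
- High arm, the quarter above 21692 IU/week: 18000/21692 = 0.83, a reduction of at least 17%.
- Low arm, the same quarter: 4000/21692 = 0.18, a reduction of at least 82%.
- Low arm, the half at 13944 IU/week or more: 4000/13944 = 0.29, a reduction of at least 71%.
- Untreated entrants: prior dose 0, so either arm is a first prescription.

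If Italian doses are lower, fewer patients have a reduction in the high arm and more have an increase. The mixture remains.

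**5. What a valid baseline interaction could show.** Let D = 1194 events and let s be the share of events in the subgroup, which the article does not give. The variance of the log ratio of hazard ratios is 4/(D·s) + 4/(D·(1 − s)). For s = 0.5 it is 16/1194 = 0.0134, standard error 0.116. A ratio of 0.80 has |ln 0.80| = 0.223, so power is Φ(0.223/0.116 − 1.96) = 49%.

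| s | Power for ratio 0.80 | Ratio detectable with 80% power |
|---|---|---|
| 0.5 | 49% | 0.72 |
| 0.3 | 42% | 0.70 |
| 0.2 | 34% | 0.67 |
| 0.1 | 21% | 0.58 |

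**The case against.** The strongest reply is that a journal article is no place for full subgroup definitions. The list opens with the word *including*, and a fuller plan may add prior dose and hemoglobin. That stands against any claim about what is merely absent. A reader might infer that ESA resistance will go unexamined; an open list cannot show that, and the feasibility outcomes on dose changes touch on responsiveness. But the reply does not cover the variable the article does name, which contradicts its own baseline label.

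Other stronger readings also fail:
- *Resistance is the trial's hypothesis.* It appears in the Background as a possibility. The Trial Hypothesis and the Aims do not mention it.
- *Pooling dose increases and reductions biases the main result.* It does not. Broad entry is a declared choice of a pragmatic trial, and the intention-to-treat contrast is a valid average over prior doses.
- *Stratifying by center only is a fault.* With 1102 per arm, the 95% range of chance imbalance for a factor of 20% prevalence is ±1.96 × √(2 × 0.2 × 0.8/1102), about ±3.3 percentage points. That is small, and a baseline modifier can be tested without being a stratification factor.
- *Baseline hemoglobin and dose are left out of the Cox model.* The article names no Cox covariates, so none is shown to be excluded.

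Two practical objections stand in part. Eligibility requires ESA status but not the prior weekly dose, so that dose may not be recorded. Interaction power is also modest, which limits what the corrected analysis can deliver.

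**Conclusion.** The point holds in this limited form. As written, the plan would use a post-randomization ESA dose as an effect modifier under a baseline label, and that subgroup cannot yield a valid treatment effect. The variables that could, prior ESA dose or status and baseline hemoglobin, are not named, although entry is mixed on both and the Background gives a reason to look at them.

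The primary comparison is unaffected. The reduction of at least 17% for about a quarter of patients in the high arm rests on US registry patients incident in 1998 and is an illustration for Italian entrants, not an estimate. The 21-49% power range rests on an assumed 10-50% share of events in the subgroup. The flaw in the on-study dose subgroup depends on neither figure; it follows from the timing of the variable.

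**What to change.** In the *Data analysis* section:
- Replace mean on-study ESA dose as an effect modifier with pre-randomization weekly ESA dose, entered as 0 for untreated patients and otherwise in epoetin equivalents.
- Add baseline hemoglobin to the modifiers.
- State that any analysis by on-study dose is descriptive and is not a comparison of the randomized arms.

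Optionally, use both baseline values as covariates in the additional Cox model, and examine their combination as an exploratory resistance subgroup with its definition fixed in advance.

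The cost is small. Prior weekly dose may need one baseline data field if it is not already recorded. The conversion to epoetin equivalents must be stated, but the trial already needs one to allocate equivalent doses of other agents. Reports should acknowledge the limited interaction power. The 2204 patients, the 1194 events, the stratification and the eligibility rules do not change.
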